# Continuous peptide-based versus sequential standard polymeric enteral nutrition formula in critically ill patients with acute gastrointestinal injury: study protocol for a single-center, parallel-group randomized controlled trial

**DOI:** 10.3389/fmed.2026.1761334

**Published:** 2026-02-10

**Keywords:** acute gastrointestinal injury, enteral nutrition, peptide-based formula, protocol, randomized controlled trial, standardpolymeric formula

## Abstract

**Background:**

In critically ill patients with acute gastrointestinal injury (AGI), early administration of a peptide-based enteral formula (PBF) may be beneficial during the acute phase. Nevertheless, after gastrointestinal function improves, it remains unclear whether continuing a PBF or switching to a standard polymeric formula (SPF) is preferable.

**Objectives:**

To compare the efficacy and safety of continuing a PBF versus switching to an SPF from day 4 onward in critically ill patients with AGI whose gastrointestinal function has recovered or improved to AGI grade I by day 4.

**Design:**

Single-center, parallel-group, randomized, controlled, trial with 1:1 allocation, intention-to-treat analysis.

**Setting:**

Three clinical units of the Department of Critical Care Medicine at the First Hospital of Jilin University (Changchun, China).

**Participants:**

We will ultimately include 496 adult critically ill patients with AGI grade I–II who meet the eligibility criteria in the final analysis.

**Interventions:**

Continuous Peptide-Based Enteral Formula Group (PBF group): patients will receive continuous infusion of a PBF, initiated within 7 days of ICU admission. Sequential Standard Polymeric Enteral Formula Group (SPF group): patients will receive a PBF during the first 3 days in the ICU and will be transitioned to an SPF if the AGI grade is 0–I on ICU day 4.

**Primary outcome measure:**

The primary outcome is the mean daily energy intake on day 7 (kcal/kg/day). An intention-to-treat analysis will be used to assess this outcome to enhance the robustness of the results. Secondary outcomes and relevant process measures will be evaluated in accordance with the study protocol.

**Clinical trial registration:**

https://www.chictr.org.cn/showproj.html?pid=139513, Identifier ChiCTR2200056858.

## Introduction

1

The successful implementation of early enteral nutrition (EN) can exert crucial physiological effects in critically ill patients by down-regulating systemic immune responses, reducing oxidative stress, and maintaining the intestinal microenvironment, thereby supporting cellular and organ function recovery, promoting wound healing, and ultimately improving outcomes (1–4). However, up to 60% of critically ill patients reportedly develop impairments in gastrointestinal digestion, absorption, motility, and barrier function, collectively termed acute gastrointestinal injury (AGI) (5, 6), leading to reduced or interrupted delivery of EN, subsequent malnutrition, and worsened prognosis (7–9). Therefore, selecting an appropriate EN strategy is particularly important in patients with AGI.

Choice of formula is a key component of the EN strategy for AGI. Peptide-based (short-peptide, oligomeric) enteral nutrition formulas (PBFs) are pre-digested and can be absorbed more rapidly in the intestine (10), whereas standard polymeric enteral nutrition formulas (SPFs) more closely approximate physiological conditions, stimulate digestive enzyme secretion, are absorbed more slowly, and may promote postprandial protein accretion (11). The Society of Critical Care Medicine/American Society for Parenteral and Enteral Nutrition (SCCM/ASPEN) guidelines recommend (12) initiating EN with an SPF in the Intensive Care Unit (ICU) and considering a PBF in patients with persistent diarrhea, suspected malabsorption, ischemia, or intolerance to a fiber-free formula. Our previous work (13) indicated that, in septic patients with AGI grade I–II, early use of a PBF was more suitable, whereas an SPF could be considered when EN initiation was delayed. However, in critically ill patients with gastrointestinal dysfunction, the optimal choice between continuing a PBF and transitioning to an SPF after gastrointestinal recovery (AGI 0–I) remains unclear. Current guidelines and available clinical studies offer no direct evidence to address this issue.

This study is designed to address this uncertainty by comparing the safety and efficacy of the two enteral nutrition strategies. The findings are expected to inform evidence-based selection of enteral nutrition formulas in patients with AGI.

## Methods and analysis

2

### Study design

2.1

This is an investigator-initiated, single-center (Department of Critical Care Medicine at the First Hospital of Jilin University), parallel-group, randomized controlled clinical trial. The trial has been registered with the Chinese Clinical Trial Registry (ChiCTR2200056858). The trial protocol was developed in accordance with the Standard Protocol Items: Recommendations for Interventional Trials (SPIRIT) statement (14). The flow diagram of patient enrollment, randomized and follow-up is shown in Figure 1. The final version of the protocol (version 1.0) was finalized on February 28, 2022.

**Figure 1 fig1:**
[figure not shown]
Flow diagram of patient enrollment, randomized and follow-up. ICU, Intensive Care Unit; SOFA, sequential organ failure assessment; AGI, acute gastrointestinal injury; ESPEN, European Society for Clinical Nutrition and Metabolism; PBF group, Continuous Peptide-Based Enteral Formula Group; SPF group, Sequential Standard Polymeric Enteral Formula Group.

### Trial committees

2.2

The trial management committee comprises representatives from the Clinical Research Department, the Department of Critical Care Medicine, and the Biobank of the First Hospital of Jilin University. A dedicated research team within the Department of Critical Care Medicine, independent of the treating clinical team and not involved in patient care, will be responsible for outcome assessment and for clinical data collection and management. The Clinical Research Department provides methodological support, including input into study design, trial oversight, and collaboration on data management and statistical analysis, while the Biobank oversees the processing, and secure storage of biological specimens.

### Study population

2.3

Adult critically ill patients admitted to the Department of Critical Care Medicine at the First Hospital of Jilin University who are eligible to initiate early enteral nutrition (within 24–48 h) and have AGI grade I–II with organ dysfunction will be screened for eligibility. After obtaining informed consent, feeding will follow the guideline-based protocol (15). On day 4, gastrointestinal function will be reassessed, and patients whose AGI has improved to grade 0–I will be randomized.

#### Eligibility criteria

2.3.1

The inclusion and exclusion criteria are as follows:

##### Inclusion criteria

(1) Age ≥18 years.(2) ICU admission with AGI grade I (gastrointestinal dysfunction with risk of failure) or grade II (gastrointestinal dysfunction) according to the 2012 European Society of Intensive Care Medicine (ESICM) (6) diagnostic criteria.(3) Able to initiate enteral nutrition within 24–48 h of ICU admission.

##### Exclusion criteria

(1) Contraindications to enteral feeding or profound hemodynamic instability precluding any form of nutritional therapy.(2) Concurrent oral intake.(3) History of chronic liver disease or severe hepatic dysfunction [Child-Pugh C (16)] (Supplementary Table S1).(4) Serum urea nitrogen increasing by >4 mmol/L per day, or renal insufficiency requiring renal replacement therapy (e.g., hemodialysis or continuous renal replacement therapy).

### Randomization and blinding methods

2.4

Because all enrolled patients initially present with AGI grade I–II, a PBF will be administered for the first 3 study days. On day 4 of the study, gastrointestinal function will be reassessed. Patients reassessed as AGI grade 0–I will be eligible for randomization. Eligible patients will be randomized using block randomization, with a 1:1 allocation ratio to either continued a PBF (PBF group) or transition to an SPF (SPF group). The randomization sequence will be generated in R software (version 4.4.2) using permuted blocks of variable size (4 and 6).

Owing to the nature of the intervention, this is an open-label protocol, and the treating clinical team must be aware of group assignment for intervention delivery (participants may or may not be aware depending on clinical status). To minimize detection bias, feeding intolerance and other outcomes will be assessed and recorded by dedicated research staff who are independent from the ICU clinical team and do not participate in treatment decisions or nursing care.

### Sample size

2.5

The sample size was estimated in PASS v23 (NCSS, Kaysville, UT; https://www.ncss.com/software/pass/) for the primary endpoint of energy intake on day 7 (kcal/kg/day), comparing two independent groups with equal allocation (1:1). Based on retrospective data, the SPF group had a mean ± standard deviation (SD) intake of 22.4 ± 9.825 kcal/kg/day and the PBF group had 24.9 ± 9.1 kcal/kg/day. Using a two-sided *α* = 0.05 and power (1 − *β*) = 0.90, the required sample size is *n* = 225 per group (total *N* = 450). Allowing for a 10% attrition rate, the target sample increases to *N* = 495. To maintain balance between the two treatment groups under block randomization with variable block sizes of 4 and 6, the final planned sample size is *N* = 496.

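### On the protocol's own inputs, 225 patients per group give 80% power, not the stated 90%

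*Protocol article*

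**What the plan says.** Protocol article, section 2.5 (Sample size), sizes the trial on day-7 energy intake. The design is described as "comparing two independent groups with equal allocation (1:1"). The planning values come from retrospective data: "the SPF group had a mean ± standard deviation (SD) intake of 22.4 ± 9.825 kcal/kg/day" and "the PBF group had 24.9 ± 9.1 kcal/kg/day". The error rates are given as "Using a two-sided *α* = 0.05 and power (1 − *β*) = 0.90". From these the section concludes that "the required sample size is *n* = 225 per group (total *N* = 450"). Then: "Allowing for a 10% attrition rate, the target sample increases to *N* = 495". After an adjustment for the randomization blocks, "the final planned sample size is *N* = 496", which is 248 per group.

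The section gives no other effect size or SD, no variance reduction from covariates, and no alternative test.

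**The concern.** Every input and the output of the calculation are printed, so it can be repeated. A difference of 2.5 against SDs of 9 to 10 is a standardised effect of about 0.26 (2.5 / 9.469). For that effect, 225 per group looks too few for 90% power and close to what 80% power requires.

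This is the design basis of the primary endpoint. If the power is overstated, the trial has a larger chance of missing its planned difference than readers are told. The trial asks whether continuing the peptide-based formula or switching to the polymeric one changes intake, so a non-significant result is a realistic outcome. It would be read as coming from a 90%-powered trial, and the evidence against a 2.5 kcal/kg/day difference would be overstated.

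**Working it through.** **Inputs (all from section 2.5).** Means 22.4 and 24.9, so the difference is 2.5 kcal/kg/day. SDs 9.825 and 9.1. Two-sided alpha 0.05 (z = 1.960). Equal allocation. Stated power 0.90 (z = 1.282). Stated n = 225 per group.

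**Step 1: sum of variances.** 9.825² + 9.1² = 96.53 + 82.81 = 179.34. The root-mean-square SD is sqrt(179.34 / 2) = 9.469.

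**Step 2: try to reproduce the stated n.** n per group = (z_alpha + z_power)² × (SD1² + SD2²) / difference².

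- 90% power: (1.960 + 1.282)² = 10.507, and 10.507 × 179.34 / 6.25 = 301.5, so 302 per group.
- 80% power: (1.960 + 0.842)² = 7.849, and 7.849 × 179.34 / 6.25 = 225.2, so 226 per group (225 if the plain mean of the two SDs is used).

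The figure of 225 is not reproduced at 90% power. It is within one patient of the 80% answer.

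**Step 3: power at 225 per group.** SE = sqrt(179.34 / 225) = 0.893. Then 2.5 / 0.893 = 2.80, and Phi(2.80 − 1.96) = Phi(0.84) = 0.80 (79.96% unrounded).

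**Step 4: check with the noncentral t distribution.** Power at 225 per group is 79.8%, with equal variances or with Welch. The first n that reaches 80% is 227; the first that reaches 90% is 303.

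**Step 5: what 225 per group would detect with 90% power.** (1.960 + 1.282) × 0.893 = 2.89 kcal/kg/day. Keeping the difference at 2.5 instead, the common SD would have to be about 8.18. Section 2.5 gives neither value.

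**Step 6: other readings of the inputs, all for 90% power.**

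| Reading | n per group |
|---|---|
| Two-sided, smaller SD (9.1) in both groups | 279 |
| Two-sided, mean of the two SDs | 302 |
| Two-sided, larger SD (9.825) in both groups | 325 |
| One-sided 0.05, root-mean-square SD | 246 |
| One-sided 0.05, SD 9.1 in both groups | 227 |

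Only the last row comes near 225. It contradicts the stated two-sided alpha and discards the SPF group's SD.

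**Step 7: the whole planned sample.** With 248 per group and no losses, power is 83.6% (normal) or 83.5% (t).

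**The case against.** The arithmetic is not open to dispute, but four points can be made against the way it is used.

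- **Origin of the error.** The document shows only that the inputs, the power and the n are inconsistent. It does not show which was misprinted. The exact 80% answer rounds to 226 or 227 rather than 225, and a wrong SD or difference cannot be excluded because the retrospective data are not shown. This stands as a caution: an 80% calculation is the likely source, not a proven one. It does not rescue the statement, since the printed figures cannot all be right.
- **The primary analysis is adjusted.** Section 2.8.2 specifies linear regression on APACHE II score, BMI, AGI grade and primary diagnosis, which could raise the real power. If these explained 10% of the outcome variance (an assumption), power at 225 per group would be about 84%: 2.80 / sqrt(0.90) = 2.95, and Phi(2.95 − 1.96) = 0.84. Reaching 90% needs about 25% explained (1 − 225 / 301.5 = 0.25). Section 2.5 makes no such assumption, so adjustment cannot justify the figure as printed. It does mean that 20% is the type II error of the unadjusted comparison described there, not necessarily that of the final analysis.
- **Losses pull the other way.** Section 2.8.3 expects about 15% missing day-7 outcomes. That leaves about 211 per group (248 × 0.85), with roughly 77% power in an unadjusted complete-case comparison. The conclusion does not depend on this.
- **Severity.** Type I error, the effect estimate and its confidence interval are unaffected, and section 2.8.2 promises cautious interpretation. That limits the harm but does not make a wrong power claim for the primary endpoint acceptable.

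**Conclusion.** The concern holds. On the inputs in section 2.5, 225 evaluable patients per group give 80% power (79.8% by the t distribution), not 90%. The type II error for a difference of 2.5 kcal/kg/day is about 20% against the stated 10%. A true 90% needs 302 to 303 evaluable per group, 34% more than stated. The conclusion rests only on the printed means, SDs, alpha and allocation and on the unadjusted two-group comparison that the section describes. No reading consistent with the stated two-sided alpha brings the requirement down to 225. The statement must be corrected.

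**What to change.** Check the sample-size software output and the retrospective inputs. If the printed means and SDs are confirmed, correct section 2.5 to say that 225 evaluable patients per group give 80% power to detect 2.5 kcal/kg/day with these SDs at two-sided alpha 0.05; equivalently, 90% power for 2.9 kcal/kg/day. Keep N = 496. The cost is one corrected sentence and a less favourable stated power, with no extra patients.

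If the sponsor wants to claim a figure near 90%, there are two honest routes:

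- Base it explicitly on the covariate-adjusted analysis, with a stated and justified proportion of variance explained (about 25% would be needed at 225 per group).
- Recalculate N. The unadjusted comparison needs about 604 to 606 evaluable patients in total before any allowance for attrition; with 10% attrition, 604 / 0.9 comes to about 672 randomized. This route is much more expensive and is not needed to make the protocol correct.

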#### Missing data and interpolation strategies

2.8.3

The proportion of missing data for the primary outcome (caloric intake on day 7) is expected to be approximately 15%, mainly due to discharge, transfer, or incomplete records. The primary analysis will be conducted in the FAS using multiple imputation (MI) under the missing-at-random (MAR) assumption. The imputation model will include treatment group, APACHE II score, BMI, AGI grade, primary diagnosis, and other variables related to missingness or the outcome.

As sensitivity analyses, a complete-case analysis (including only participants with observed day-7 outcomes) will be performed. In addition, PPS analysis and delta-adjusted MI analyses will be conducted to assess the robustness of the results under alternative missing data assumptions.

If the results are consistent across analyses, the study findings will be considered robust.

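### The sample size allows for 10% loss but the missing-data section expects about 15%, so 496 randomised patients give about 422 observed Day-7 outcomes, not the planned 450

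*Protocol article*

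**What the plan says.** Section 2.5 (Sample size) sizes the trial on Day-7 energy intake, "comparing two independent groups with equal allocation (1:1"). The inputs are an SPF "intake of 22.4 ± 9.825 kcal/kg/day" and "the PBF group had 24.9 ± 9.1 kcal/kg/day". "Using a two-sided *α* = 0.05 and power (1 − *β*) = 0.90", it concludes that "the required sample size is *n* = 225 per group (total *N* = 450"). It continues: "Allowing for a 10% attrition rate, the target sample increases to *N* = 495". The total is then raised to 496 to suit the block sizes.

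Section 2.8.3 (Missing data and interpolation strategies) says: "The proportion of missing data for the primary outcome (caloric intake on day 7) is expected to be approximately 15" per cent. It names discharge, transfer and incomplete records as the main causes. The primary analysis there is multiple imputation under missing at random in the Full Analysis Set (FAS), with a complete-case analysis as a sensitivity check. Besides treatment group and four named covariates, the imputation model may take in further, unnamed variables.

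Section 2.8.2 (Data analysis) admits to the FAS only randomised patients whose Day-7 value is observed or can be derived. The abstract says: "We will ultimately include 496 adult critically ill patients with AGI grade I–II who meet the eligibility criteria in the final analysis".

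**The concern.** The allowance in section 2.5 has one purpose: to leave 225 patients per group with the primary endpoint after losses. Section 2.8.3 forecasts a higher loss on that same endpoint and does not say why the two rates differ. On the protocol's own forecast, the planned number of observed outcomes is not reached.

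The primary comparison would then be less precise than the sample-size section implies, and a null result would be judged against a number of outcomes that the plan itself does not expect. A reader also cannot tell from the text how many observed values will support the primary result.

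**Working it through.** **Inputs.** From section 2.5: means 22.4 and 24.9, so the difference is 2.5 kcal/kg/day; SDs 9.825 and 9.1; two-sided α 0.05; 225 per group; 10% loss; final N 496. From section 2.8.3: about 15% missing.

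**Step 1: the plan's inflation.** 450 × 1.10 = 495 reproduces the stated figure. To have 450 left after losing a fraction d, the number needed is 450/(1 − d). At d = 0.10 this is 450/0.90 = 500. With 496 randomised, 10% loss leaves 496 × 0.90 = 446.4, about 446.

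**Step 2: the plan's missing-data forecast.** 496 × 0.85 = 421.6, about 422, or 210.8 (about 211) per group. The shortfall is 450 − 422 = 28. Keeping 450 observed at 15% missing would correspond to 450/0.85 = 529.4, that is 530 randomised, 34 more than planned.

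**Step 3: effect on power.** Normal approximation, unadjusted comparison of two means with n observed per group:

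power = Φ( 2.5 / √(V/n) − 1.96 ), where V = 9.825² + 9.1² = 96.53 + 82.81 = 179.34.

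| Scenario | n per group | 2.5/√(V/n) | Power |
|---|---|---|---|
| Planned | 225 | 2.80 | 80.0% |
| 496 with 10% loss | 223.2 | 2.79 | 79.6% |
| 496 with 15% missing | 210.8 | 2.71 | 77.4% |

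A t-based calculation with unequal variances gives 79.8%, 79.5% and 77.2%.

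**Step 4: splitting the loss.** Multiplying instead of dividing costs 80.0 − 79.6 = about 0.3 points before rounding. Going from 10% to 15% costs a further 79.6 − 77.4 = 2.2 to 2.3 points. The total is about 2.6 points. The standard error of the difference grows by √(225/210.8) = 1.033, about 3%.

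**Step 5: why the starting point is 80%, not 90%.** The required n per group is (1.96 + z)² × 179.34 / 2.5². With z = 1.2816 (90% power) this is 301.5, so 302. With z = 0.8416 (80% power) it is 225.2, so 226. The stated 225 therefore corresponds to about 80% power on the stated inputs. That discrepancy exists at any loss rate and is a separate matter.

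**The case against.** **Imputation keeps everyone.** Because the primary analysis imputes, 422 is the number observed, not the number analysed. Section 2.8.3 leaves room for auxiliary variables, and the trial collects candidates: daily feeding-intolerance status on days 4 to 7 and feeding hours from Day 4. These could recover some precision. That stands, so it would be wrong to say that imputation recovers nothing. But the article names no auxiliary variable for the imputation model and quantifies none, so full recovery cannot be assumed. The complete-case analysis would rest on about 422 in any case.

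**Attrition and missing outcome may be different quantities.** The article does not define them as the same, and withdrawal could be narrower than absence of a Day-7 record. This makes the mismatch an unexplained difference more than a slip in arithmetic. It does not remove it, because the only job of the allowance in section 2.5 is to protect the number with the primary endpoint. If the two losses were separate and cumulative (an assumption), fewer would remain: 496 × 0.90 × 0.85 = about 379.

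**The abstract's 496 is not clearly a contradiction.** A reader might infer a third conflicting count. Under intention-to-treat with imputation, it can simply mean that all randomised patients are analysed. What it does not fit is the FAS definition in section 2.8.2, which leaves out a patient whose Day-7 value is neither observed nor derivable. Imputing within such a set fits poorly too.

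**Covariate adjustment may regain power.** It may. The article gives no R² from which to judge how much, and section 2.5 is itself an unadjusted calculation.

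**Conclusion.** The inconsistency is real and the figures are checkable: 10% in section 2.5, about 15% in section 2.8.3, and about 422 observed outcomes (211 per group) where 450 (225 per group) were planned. Unadjusted power falls by 2 to 3 points, from 80.0% to about 77%. Nearly all of that comes from the change in loss rate; the multiplication rule contributes about 0.3 points.

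A reader might infer that missing data explains the whole distance from the stated 90% to 77%. The documents do not support that. About 10 points of it are already present at 225 per group with no loss at all.

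The result rests on the stated means and SDs, on 15% missing spread equally over the arms, on an unadjusted comparison, and on no precision being regained through auxiliary variables or covariates. The defect is moderate: it does not threaten the design, but it misstates a number on which the primary analysis relies and should be corrected.

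**What to change.** - **Sections 2.5 and 2.8.3:** use 15% in both. Keep 496 and describe it as the number randomised.
- **Section 2.5:** drop the claim that 450 will be evaluable. State about 422 expected observed Day-7 outcomes (496 × 0.85) and the unadjusted power at that number, about 77% on the stated inputs. The 450 target has to go explicitly: 15% loss, division by (1 − loss), 450 observed and N = 496 cannot all hold, since 450/0.85 gives 530. Remove the 450 × 1.1 step.
- **Abstract and section 2.8.2:** reconcile the abstract's 496 in the final analysis with the FAS definition. Either the primary set is all randomised patients with imputation, or it is those with an observed or derivable value and the abstract gives 496 as randomised only.

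The cost is revised text in four places and a less favourable stated power. No extra enrolment is needed. If the base calculation is also corrected for its 90% claim, the power figure should be restated once, with both corrections made together.
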